### Baseline Survey

A structured baseline survey questionnaire will be developed to measure students’ mental health outcomes. The questionnaire will include the 10-item Perceived Stress Scale (PSS-10), 7-item Generalized Anxiety Disorder (GAD-7) scale, 9-item Patient Health Questionnaire-9 (PHQ-9) scale, and WHO-5 (World Health Organization-Five Well-Being Index) scale to measure SAD and well-being [20,49,51-53]. These tools have been validated for making comparisons between population subgroups [35]. The questionnaire will also include sociodemographic and economic variables, including age, relationship status, religion, orphanhood status [54], college, sponsorship status, working status, living arrangement, year of study, and current academic performance among others. Participant data will be collected online through self-administered questionnaires on the ResilienceNHope platform [43]. The data will be hosted online on the ResilienceNHope server and downloaded for analysis.

### Follow-Up Surveys

A follow-up survey questionnaire will be used to assess improvements in the students’ mental well-being using validated scales for SAD, using the PSS-10, GAD-7, and PHQ-9. These surveys will be conducted at 1 month, 3 months (mid-term evaluation), and 6 months of the study (endline evaluation). The app has automated email reminders at 6 weeks, 3 months, and 6 months to boost completion rates. In addition, receiving daily messages with images is an incentive to students, and this was tested during the cocreation process with students.

The questionnaire will also include variables on participants’ satisfaction with the W4S program intervention and suggested improvements and recommendations. Participant data will be collected and hosted online through self-administered questionnaires on the ResilienceNHope web platform [43] and downloaded for analysis. We recognize that retention is and has been a challenge for online surveys; part of the mitigation strategy is to make the survey shorter. The number of questions was reduced to the bare minimum.

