### Aims of the Study

This study aims to determine the prevalence and correlates of SAD among university students in Uganda. It also aims to determine if daily supportive text messages can help reduce the prevalence of SAD and improve well-being among university students.

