### Specific Objectives

This study has the following objectives: (1) to determine the prevalence and correlates of SAD among university students in Uganda, (2) to investigate the effectiveness of the daily W4S supportive messages in reducing levels of SAD and in improving well-being among university students in Uganda, and (3) to investigate the participants’ experience and satisfaction associated with the W4S daily SMS text messaging support.

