### Midterm and Endline Evaluation

The program will be evaluated at 1 month, 3 months (mid-term), and 6 months (endline evaluation) after the students start receiving daily supportive email and WhatsApp messages. The midterm and endline surveys will assess improvements in the students’ mental well-being using validated scales for the primary outcomes: SAD [20,48-51,53].

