### Outcomes and Measures

Primary outcome measures at baseline, 1 month, 3 months, and 6 months will be the mean difference in scores on the PSS-10, GAD-7 scale, and PHQ-9 [49,56-58]. Prevalence estimates for SAD will be calculated as the total number of undergraduate students assessed as likely to have a particular condition divided by the total number of students who completed the baseline survey. In addition, proportions for survey uptake, response rates, and completion rates will be calculated. Finally, the outcomes related to the feasibility or acceptance of the tool, along with measures of engagement and adherence, will be collected at the end of the follow-up survey.

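### Improving well-being is part of Objective 2, but the only well-being scale (WHO-5) is listed at baseline and at none of the three follow-up surveys

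*Protocol article*

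**What the plan says.** Two sections of the protocol article make well-being a target of the intervention. Aims of the Study asks whether the messages can "help reduce the prevalence of SAD and improve well-being among university students". Objective 2, under Specific Objectives, is "to investigate the effectiveness of the daily W4S supportive messages in reducing levels of SAD and in improving well-being among university students in Uganda". Both name well-being beside SAD, as something separate from it.

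The Baseline Survey section lists four scales: the PSS-10, the GAD-7, the PHQ-9 "and WHO-5 (World Health Organization-Five Well-Being Index) scale to measure SAD and well-being". The WHO-5 is the only well-being instrument named anywhere in the article.

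The Follow-Up Surveys section covers months 1, 3 and 6 and says these surveys will assess improvement in students' "mental well-being using validated scales for SAD, using the PSS-10, GAD-7, and PHQ-9". It adds that the questionnaire was deliberately shortened to help retention. Midterm and Endline Evaluation refers to "validated scales for the primary outcomes: SAD". In Outcomes and Measures, the primary outcome at all four time points "will be the mean difference in scores on the PSS-10, GAD-7 scale, and PHQ-9". Statistical Analysis plans paired t tests and proportion tests for SAD scores and SAD prevalence. None of these sections mentions the WHO-5 or any other well-being outcome.

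**The concern.** A claim that an intervention improved well-being in a single-group before-after study needs a well-being score before and after. The plan collects the first and, by its own list, not the second.

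The Follow-Up Surveys section uses the word well-being for what the PSS-10, GAD-7 and PHQ-9 will show. Those scales measure perceived stress, anxiety symptoms and depressive symptoms, and the protocol itself assigns well-being to a different instrument. If the wording stays, the second target of Objective 2 could end up being answered with the measures of the first.

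No analysis can repair this afterwards. Multiple imputation, which the plan proposes for missing items, has nothing to work from when an instrument was given to nobody at follow-up. A follow-up wave that has passed cannot be collected again.

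**Working it through.** The plan states no figure on this point, so the check is a comparison of instruments by survey, using the scale lists in Baseline Survey and Follow-Up Surveys.

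| Survey | PSS-10 | GAD-7 | PHQ-9 | WHO-5 | Scale items |
|---|---|---|---|---|---|
| Baseline | yes | yes | yes | yes | 10 + 7 + 9 + 5 = 31 |
| 1 month | yes | yes | yes | not listed | 10 + 7 + 9 = 26 |
| 3 months | yes | yes | yes | not listed | 26 |
| 6 months | yes | yes | yes | not listed | 26 |

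1. **Data for a change score.** A paired change needs the same scale at baseline and at one or more follow-ups. The WHO-5 is listed at 0 of 3 follow-ups, so the number of paired WHO-5 observations is zero, whatever the enrolment or retention.

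2. **Could the follow-up list be shorthand?** The two lists stand in adjacent sections and each names its scales. The follow-up section describes its scales as SAD scales and says the number of questions was cut. Midterm and Endline Evaluation, Outcomes and Measures, and the before-after part of Statistical Analysis agree with the shorter list. Nothing in the Methods points to the WHO-5 after baseline.

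3. **Burden of adding it.** Five items on top of 26 is 5/26 = 19% more scale items per follow-up survey, the same 31 that participants answer at baseline.

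4. **Effect on sample size.** The plan gives 90 for the before-after comparison at 80% power and two-sided 5% significance. Reading the 30% effect as a standardised paired difference of 0.30 (an assumption, since the article does not define it), the normal approximation is ((1.96 + 0.84)/0.30)² ≈ 87.2, and the exact paired t test gives 89.1, rounded up to 90. That reproduces the plan's figure. It is not tied to any one scale, so adding the WHO-5 as a secondary outcome does not require it to change. The prevalence target of 2247 and the enrolment target of 4494 concern SAD at baseline and are also untouched.

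**The case against.** The strongest counter-argument is the abstract. It lists data collection at baseline, 1, 3 and 6 months and then says that the questionnaires cover SAD and well-being, with no limit to baseline. On that reading the WHO-5 is meant at every survey and the follow-up list is incomplete. The full questionnaires are not shown, and the article says the survey instrument is already finished, so its content may differ from one sentence in the Methods. This stands in part: it cannot be said with certainty that the data will be missing. It does not remove the problem. The abstract names no well-being scale and does not say that well-being is repeated, while the Methods give an explicit list without it. If the abstract is right, Follow-Up Surveys is wrong; if the Methods are right, Objective 2 promises something unmeasured. Even on the kinder reading, no well-being outcome is defined.

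A second argument is that well-being is subordinate. The abstract's objective, the primary outcomes, the sample size and the hypotheses all concern SAD. That is fair, and no SAD estimate is biased by this gap. But well-being is in the aim and in a numbered objective, and no outcome of any rank serves it.

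Third, the use of well-being in the follow-up sections may be only a loose phrase, since the scales are named straight after it. Nothing says that symptom scores will be reported as a well-being result, so that is a risk of the wording and not a stated plan.

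Finally, the change is not free: the instrument is complete, ethical approval is in place, and the survey was shortened to protect retention.

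**Conclusion.** The concern holds. As the Methods are written, the WHO-5 is given once, no change in well-being can be computed, and one of the two stated targets of Objective 2 cannot be answered. The loss for that target is complete (0 of 3 follow-up surveys). The SAD target is not affected.

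The conclusion rests on taking the explicit scale list in Follow-Up Surveys at face value. If the questionnaires in use already contain the WHO-5 at follow-up, the data problem disappears. What remains is a contradiction between sections and an undefined outcome, both of which still need correcting. Because roll-out is scheduled for March 24, 2026 and the first follow-up falls one month after enrolment, this should be settled before the first follow-up survey goes out.

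**What to change.** Either of two changes resolves it.

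- **Keep the well-being target.** Add the WHO-5 to the 1-, 3- and 6-month questionnaires in Follow-Up Surveys. In Outcomes and Measures, list change in WHO-5 score from baseline to 6 months as a secondary outcome. In Statistical Analysis, name it alongside the SAD scores in the paired comparisons already planned.
- **Keep the shorter survey.** Remove improvement in well-being from Aims of the Study and Objective 2, and describe the WHO-5 as a baseline measure only.

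In both cases, bring the abstract into line, and reword Follow-Up Surveys and Midterm and Endline Evaluation so that the PSS-10, GAD-7 and PHQ-9 are described as measures of stress, anxiety and depression and not of well-being.

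The first option costs five items per follow-up survey on an online form (26 to 31 scale items, about 19% more), an update to a finished instrument, and whatever notification the ethics committee requires, with some possible effect on completion. The second costs only wording. Neither changes the stated sample sizes.

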### Participants’ Recruitment and Subscription

This study will be conducted among Makerere University students in Kampala, Uganda. We will consider currently enrolled students from year 1 to year 3 of study. We have made an assumption that all university students own smartphones based on a previous study [55]. Internet access is always guaranteed to all university students during the semester when the study will be implemented. We will broadcast information about the study through social media platforms used by university students, including WhatsApp, emails, and Twitter (subsequently rebranded X). We will also share information about the study through posters and by word-of-mouth within accessible groups. We will also engage the staff of the Counselling and Guidance Center at the University Hospital to inform students about this study.

During the broadcast, students will be informed about the possibility of being enrolled in a digital intervention program (W4S program). The study will be launched through an announcement by the office of the Dean of Students of Makerere University, the Students’ Guild, and the Director of Makerere University Hospital. All interested students will be provided with a link to the W4S website to self-subscribe to the study. Potential respondents will be asked to register for the study with their active emails and also consent to being part of the study. Once they have electronically consented to the study, they will receive another link to the baseline study. The cocreated and adapted messages will be sent to subscribers’ email and WhatsApp daily at 7 AM East African Time. Each subscriber will receive the W4S program daily for 6 months.

### Midterm and Endline Evaluation

The program will be evaluated at 1 month, 3 months (mid-term), and 6 months (endline evaluation) after the students start receiving daily supportive email and WhatsApp messages. The midterm and endline surveys will assess improvements in the students’ mental well-being using validated scales for the primary outcomes: SAD [20,48-51,53].

### Outcomes and Measures

Primary outcome measures at baseline, 1 month, 3 months, and 6 months will be the mean difference in scores on the PSS-10, GAD-7 scale, and PHQ-9 [49,56-58]. Prevalence estimates for SAD will be calculated as the total number of undergraduate students assessed as likely to have a particular condition divided by the total number of students who completed the baseline survey. In addition, proportions for survey uptake, response rates, and completion rates will be calculated. Finally, the outcomes related to the feasibility or acceptance of the tool, along with measures of engagement and adherence, will be collected at the end of the follow-up survey.

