### Sample Size Estimation

The total student population at Makerere University, Kampala, Uganda, is about 35,000 [41]. It is estimated that the sample size needed for our prevalence estimates with an expected SAD prevalence of 50% [10,12], a 95% interval, and a 2% margin of error for moderate-to-high stress, moderate-to-high anxiety, and moderate-to-high depression among Makerere University students will be 2247. A sample size calculator was used to determine the sample size [28,59,60].

Based on the previous maximum survey completion rates of 50% observed in similar programs, a minimum of 4494 students will be enrolled in the W4S email and WhatsApp messaging program over 6 months to obtain an estimated 2247 students’ completion at baseline. To achieve a power of 80% (*β*=.2) and a 2-sided significance level of 5% (*α*<.05) and to detect an effect size of 30% before and after the intervention, a sample size of 90 would be needed [49].

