### Statistical Analysis

Once data are downloaded from the W4S server, the data from the baseline and follow-up surveys will be exported to STATA version 17 for data analysis. Observations with more than 50% missing responses will be omitted from the dataset. Otherwise, missing data on individual variables will be handled using multiple imputation with baseline and postbaseline variables [61].

At baseline, frequency distributions will be used to summarize categorical variables, while means and SDs will be used for continuous variables. Chi-square tests and/or *F* statistics will be used to measure the association between demographic characteristics and SAD variables. Multivariable logistic regressions will be used to determine the correlates of SAD among MAK undergraduate students. We plan to conduct rural-urban disaggregated analysis to account for diversity among the students.

Paired sample 2-tailed *t* tests and proportion tests will be used to assess significant differences in mean scores and prevalence rates of SAD at baseline, 1 month, 3 months, and 6 months. Profile plots of mean scores will be generated while controlling for background characteristics. All findings will be reported at 95% CI with a significance level of 5% (*P*<.05). The data will be analyzed using Stata version 17.

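### Three primary scales at three follow-up times are each tested at 5% with no lead scale or time point, and the sample size of 90 is a single-test figure for an undefined effect

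*Protocol article*

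**What the plan says.** Under Outcomes and Measures, the Protocol article says: "Primary outcome measures at baseline, 1 month, 3 months, and 6 months will be the mean difference in scores on the PSS-10", followed by GAD-7 and PHQ-9. It ranks neither the scales nor the times. Midterm and Endline Evaluation also treats stress, anxiety and depression together as the primary outcomes.

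Under Statistical Analysis: "Paired sample 2-tailed *t* tests and proportion tests will be used to assess significant differences in mean scores and prevalence rates of SAD" across the four survey times. The same section closes with "All findings will be reported at 95% CI with a significance level of 5" percent. It gives no hierarchy, adjustment or success rule.

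Under Sample Size Estimation, the before-after calculation uses 80% power, "a 2-sided significance level of 5" percent, and concludes that "to detect an effect size of 30% before and after the intervention, a sample size of 90 would be needed". The enrolment target comes from a separate calculation for prevalence precision: 4494 enrolled, to give 2247 who complete the baseline survey.

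**The concern.** Effectiveness in reducing stress, anxiety and depression is one of the three specific objectives. It is to be judged by significance tests against baseline. With three scales and three follow-up times of equal standing, each tested at 5%, the error rate for the primary question as a whole is well above 5%. Nothing in the article says which result, or how many, would count as evidence of effect, so an isolated significant result could be given weight after the event.

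The sample size statement does not match this structure. It gives power for one comparison, while the primary outcome section describes nine. Its effect measure is a percentage with no stated base, so a reader cannot tell whether it means a standardized mean change, a relative fall in a score or a relative fall in prevalence.

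**Working it through.** **Inputs from the article.** Three primary scales; follow-up at 1, 3 and 6 months; 5% two-sided for every finding; 80% power; effect size 30%; n = 90; 4494 enrolled and 2247 baseline completers.

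**Assumptions.** The 30% is read as a mean change of 0.30 SD of the change score, because no SD is given. Correlations between scales and between times are not given, so a range is shown.

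**1. Reproducing n = 90.** For one paired t test, the normal approximation is n = (1.960 + 0.842)² / 0.30² = 87.2, so 88. The exact noncentral t calculation gives n = 90, with 80.4% power at 90. The stated figure is therefore right for one test under this reading.

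**2. Number of primary tests.** 3 scales × 3 follow-up times = 9 comparisons with baseline.

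**3. Family-wise error if nothing changes.** With independent tests: 1 − 0.95⁹ = 37.0%. With correlated tests, nine standard normal statistics were simulated (400,000 draws). The correlation between any two was the product of the time and scale correlations, and each statistic was compared with ±1.96. The chance of at least one significant result was:

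| Correlation between times | Scales 0.5 | Scales 0.6 | Scales 0.7 |
|---|---|---|---|
| 0.5 | 29.4% | 27.9% | 25.9% |
| 0.7 | 25.7% | 24.5% | 22.6% |
| 0.8 | 23.3% | 22.1% | 20.4% |

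Even the lowest entry is about four times the nominal 5%.

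**4. Choosing a time point is not enough.** Three scales at one time, each at 5%, give 1 − 0.95³ = 14.3% if independent. A rule across the scales is still needed.

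**5. Power if the level is divided** (noncentral t, 0.30 SD of the change score):

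| Two-sided level | Power with 90 pairs | Pairs for 80% power |
|---|---|---|
| 5% | 80.4% | 90 |
| 5%/3 | 65.8% | 120 |
| 5%/9 | 50.5% | 150 |

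**6. Practical reach.** One tenth of the 2247 baseline completers is about 225 pairs. That number gives 95.4% power even at 5%/9. The article does not state how many students it expects to complete follow-up.

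**The case against.** The case on the other side has several parts.

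- **The sample size is not wrong.** A reader might infer that 90 fails to deliver the stated 80% power. The article does not support that: 90 pairs give 80.4% for the single test described, and the lower values arise only under an adjustment the plan does not make. Ninety is also not the recruitment target. This stands. What remains is that the figure covers one test and its effect is undefined.
- **The 30% may mean something else.** Taking it as a relative fall from the article's own planning prevalence of 50% (50% to 35%), a McNemar test needs about 89 pairs at a within-person correlation of 0.5, and about 172 at zero. So the standardized reading is not the only one that leads to about 90. This stands, and it adds to the case for a definition. Larger pair counts obtained by starting from 22% rest on a prevalence that the article cites for medical students and does not use for planning.
- **Prevalence tests.** A reader might count these as nine more tests and quote 1 − 0.95¹⁸ = 60%. That assumes prevalence is independent of the scores from which it is derived, so it is not a fair figure. A reader might also infer that the proportion tests will ignore pairing and give intervals of the wrong width. The article does not name the test, and the word for pairing may govern both kinds of test, so this cannot be concluded.
- **This is a pilot in a condensed article.** Study Design describes preliminary work towards a randomized trial, and no success rule is stated, so one cannot say that a single significant scale would be declared proof. That is fair. But the article does not leave the significance level open: it fixes 5% for all findings and gives every scale and time equal primary status. Effectiveness also remains a stated objective.

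**Conclusion.** The point holds as a matter of multiplicity and of how the sample size is described. The nine primary mean-score tests carry a family-wise error of 37% if independent, and of about 20% to 29% under assumed correlations of 0.5 to 0.8 between times and 0.5 to 0.7 between scales. The exact value depends on correlations the article does not give, but over the range considered it stays far above 5%.

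The figure of 90 is sound for one two-sided paired t test at 5% with a mean change of 0.30 SD of the change score. It does not describe power for the primary family, and the article does not define the effect in those terms. Power is unlikely to be the binding problem, given planned enrolment. The weakness is in which result counts and at what level.

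**What to change.** Four changes of wording, with matching analysis code:

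1. In Outcomes and Measures, name the change from baseline to 6 months as the primary time point for PSS-10, GAD-7 and PHQ-9.
2. In Statistical Analysis, test these three changes with Holm's procedure at an overall two-sided 5%. Other multiplicity rules would also serve, but one should be fixed in advance.
3. Label the 1-month and 3-month changes and all prevalence changes as secondary, reported as estimates with 95% intervals.
4. In Sample Size Estimation, define the effect as 0.30 SD of the change score. State that 90 pairs give 80% power for a single test at 5%, and that 120 students with both baseline and 6-month scores give 80% power at 5%/3, the strictest Holm step.

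The cost is small. The stated minimum rises by 120 − 90 = 30 analysed pairs, far below the 4494 to be enrolled, and there are fewer confirmatory tests. The change should be recorded before follow-up scores are examined.

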### Hypotheses

We hypothesize that the W4S email and WhatsApp messaging program will reduce the prevalence and severity of SAD among Makerere University students. We also hypothesize that the prevalence of moderate-to-high stress, moderate-to-high anxiety, and moderate-to-high depression would be comparable to the prevalence of these conditions reported among university students in East Africa (Kenya and Tanzania) and in other jurisdictions. Finally, we hypothesize that demographic factors, socioeconomic factors, organizational factors, and class size will be associated with SAD among students.

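### The only prevalence formula divides by baseline-survey completers, yet prevalence is tested at 1, 3 and 6 months; used as written at follow-up, it would turn dropout into an apparent fall.

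*Protocol article*

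**What the plan says.** Outcomes and Measures in the protocol article gives a single prevalence formula. The numerator is "the total number of undergraduate students assessed as likely to have a particular condition", with no time point attached. This is "divided by the total number of students who completed the baseline survey". The sentence before it lists baseline, 1, 3 and 6 months, but for the primary outcome measures, which "will be the mean difference in scores on the PSS-10, GAD-7 scale, and PHQ-9".

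Statistical Analysis plans paired t tests and proportion tests for "significant differences in mean scores and prevalence rates of SAD at baseline, 1 month, 3 months, and 6 months". Hypotheses states that the programme "will reduce the prevalence and severity of SAD among Makerere University students". No other denominator for prevalence appears in the article.

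Two further statements bear on the point. Follow-Up Surveys says: "We recognize that retention is and has been a challenge for online surveys". Statistical Analysis drops observations that lack more than half of their responses, and multiply imputes other missing values on individual variables.

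**The concern.** One formula is stated, and prevalence is compared at four time points. For baseline the denominator is right, because everyone in it has been assessed. At follow-up it is not. A student who skips the 3-month survey cannot be assessed as likely to have a condition at 3 months, so cannot enter the numerator, but did complete the baseline survey and so remains in the denominator. In effect the student is scored as a non-case.

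Lowering prevalence is a declared aim (Abstract, Aims of the Study) and half of the first hypothesis. The study has no control group, so nothing in the design would reveal a fall produced by the denominator alone. Study Design says the results are meant to support an application for a larger randomized trial, and the article's Conclusions look to policy use. A spurious fall in prevalence would carry into both.

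**Working it through.** **Inputs from the article**
- Expected prevalence 50%, 95% interval, margin 2%, population about 35,000 (Sample Size Estimation).
- Baseline completers 2247, from 4494 enrolled at 50% completion (Sample Size Estimation).
- Prevalence of 22% in an earlier study of medical students at the same university (Background), used as a lower value.

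**Input assumed**
- Follow-up retention r, taken as 90%, 80%, 50% and 20%. The article gives no follow-up retention. Its 50% is completion at baseline, and the figure of below 20% in Strengths and Limitations is a general response rate for web surveys.

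**Step 1: the plan's own figure.**
n0 = 1.96² × 0.5 × 0.5 / 0.02² = 2400.9.
With the finite population correction: 2400.9 / (1 + 2399.9/35,000) = 2246.8, rounded up to 2247.
Enrolment: 2247 / 0.5 = 4494.
Both stated figures reproduce. The sample size is therefore tied to baseline completers, the same group as the prevalence denominator.

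**Step 2: the formula applied at follow-up.**
Let true prevalence p stay constant and let dropout be unrelated to case status. Cases counted at follow-up = 2247 × r × p. Dividing by 2247 gives reported prevalence = p × r, so the relative fall equals the dropout fraction, 1 − r.

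**Step 3: size.**
Comparison with baseline by a pooled two-proportion test: z = (p − pr) / √[2 p̄(1 − p̄)/2247], with p̄ = (p + pr)/2.

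| True prevalence | Assumed retention | Prevalence on baseline denominator | Fall (points) | z | Prevalence among respondents |
|---|---|---|---|---|---|
| 50% | 90% | 45% | 5 | 3.4 | 50% |
| 50% | 80% | 40% | 10 | 6.7 | 50% |
| 50% | 50% | 25% | 25 | 17.3 | 50% |
| 50% | 20% | 10% | 40 | 29.3 | 50% |
| 22% | 90% | 19.8% | 2.2 | 1.8 | 22% |
| 22% | 80% | 17.6% | 4.4 | 3.7 | 22% |
| 22% | 50% | 11% | 11 | 9.9 | 22% |

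Worked case, 50% prevalence and 90% retention: p̄ = 0.475, standard error = √(2 × 0.475 × 0.525/2247) = 0.0149, z = 0.05/0.0149 = 3.4.

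**Step 4: least dropout that reaches significance.**
At p = 50%, 5.9% dropout gives 0.5 × 0.941 = 47.05%, a fall of 2.95 points, and z = 0.0295/0.0149 = 1.98. About 6% dropout is therefore enough for P<.05. At 22% prevalence, 10% dropout does not reach it (z = 1.8).

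The test treats the time points as independent samples and ignores that the same students are measured twice, so the z values are indicative only.

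**The case against.** The strongest reply is that the sentence defines baseline prevalence only. Study Design says the baseline survey is there to estimate prevalence. Specific Objectives separates prevalence and correlates (objective 1) from effectiveness, which is worded as levels of SAD (objective 2). Sample Size Estimation sizes the prevalence estimate on baseline completers, the same denominator. The four time points in the preceding sentence belong to mean scores. This is a fair reading, and on it the formula is correct. A reader might infer that the plan counts every dropout as a non-case; the article nowhere says so, and that stronger claim is not supported.

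What the reply does not settle is the follow-up comparison. Statistical Analysis tests prevalence at three later time points, and the one denominator on the page does not fit them. This goes beyond detail left to an analysis plan, because a denominator is stated, without limiting it to baseline.

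A second reply is that the missing-data rules prevent the artefact. They might, but they do not clearly do so. A student who misses a whole survey has every response of that wave missing. If an observation is one student at one wave, the record is omitted rather than imputed, while the prevalence formula still counts the student in the denominator. If an observation is a whole student, a student removed by the rule is no longer in the data although the formula counts all baseline completers, and the two sections disagree. If the word paired is meant to cover the proportion tests too, non-responders leave both sides and the artefact disappears; the wording leaves this open.

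A third reply stands in full: the primary outcomes are mean score differences, which this denominator does not touch.

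**Conclusion.** The point holds in conditional form. The only stated prevalence denominator is right for baseline and does not fit the 1-, 3- and 6-month comparisons that the plan makes. Applied as written at follow-up, without imputing missed surveys, it produces a relative fall equal to the dropout fraction when no student has changed: from 50% to 45%, 40% and 25% at assumed retention of 90%, 80% and 50%.

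These sizes rest on constant true prevalence, dropout unrelated to case status, 2247 baseline completers and assumed retention levels. The 2% margin in Sample Size Estimation is the precision of the baseline estimate and is not a yardstick for change over time.

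A reader might also infer that the effectiveness results as a whole are compromised. They are not on this account: only the prevalence comparison is exposed. It is still worth correcting before analysis, since a reduction in prevalence is a stated aim and hypothesis.

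**What to change.** 1. In Outcomes and Measures, limit the present formula to baseline prevalence.
2. Add a definition for every visit: prevalence at time t is the number of students at or above the scale's cut-off at t, divided by the number with a valid score on that scale at t.
3. In Statistical Analysis, test the change in prevalence within person. Either McNemar's test on matched baseline and follow-up pairs or a repeated-measures logistic model (GEE or mixed) would do.
4. In the same section, say whether a survey missed in full is omitted or imputed, and whether the 50% rule applies per survey or per student. If missed surveys are imputed, all baseline completers may serve as the denominator, because each then has a case status at t.

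The cost is a few sentences and the matching analysis code; no data collection changes. Matched pairs would number about 1124 at 50% retention (2247 × 0.5) and 449 at 20% (2247 × 0.2). The reported fall in prevalence may be smaller. A respondent denominator removes the mechanical fall but not bias from selective dropout: if students with symptoms are more likely to stop responding, prevalence among respondents will still fall. The report should therefore show retention at each visit, split by baseline case status.
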